## Discussion

This clinical trial will assess the physiologic sleep variables, masticatory function of the masseter and anterior temporalis bilateral muscles, and salivary parameters by means of PSG, sEMG, and specific salivary tests (cortisol levels, presence of *P. aeruginosa,* salivary flow, and pH) respectively, prior to and after mandibular advancement oral appliance (OA_m_), neuromuscular electrical stimulation (NMES), and mastication apparatus (MA) therapies in patients with Down syndrome. As the primary outcome, the authors believe that OA_m_, neuromuscular electrical stimulation, and mastication apparatus therapies may improve masticatory and oral pharynx muscle modulation, adjusting them to a level close to normality, which may lead to a balanced muscle activity contributing to reduce snoring/sleep apnea. Good sleep quality is likely to reduce corporal stress, as shown by the decrease in cortisol levels in the saliva, as a secondary outcome. In addition, the authors expect an improvement in other salivary parameters, as the absence of snoring and/or sleep apnea, which result from the act of breathing through their mouth, will contribute to the balance of the microorganisms in the oral cavity. Moreover, polysomnography will be used to evaluate the other sleep variables and the authors believe that sleep quality will improve after all therapies have been carried out. Another expected outcome is to measure the objective compliance and adherence to the OA_m_ with an embedded microsensor thermometer.

It is important to highlight that none of these therapies will cause any injuries to the participants, so the hypothesis of harm or of adverse side effects does not apply to the present study.

Neuromuscular electrical stimulation (NMES) may produce a feeling of discomfort due to the electrical stimulus applied on masticatory muscles; however, it does not offer foreseeable risks. The mastication apparatus (MA) does not produce discomfort or foreseeable risks. The mandibular advancement oral appliance (OA_m_) embedded with a thermosensitive microchip may initially produce discreet dental and muscular discomfort, with possible temporary hypersalivation and risks of occlusal changes. The polysomnography, surface electromyography, and specific salivary tests do not produce discomfort or foreseeable risks.

These proposed therapies may contribute to an improvement in speech, swallowing, and mastication, as well as an improvement in physiologic sleep variables such as oxyhemoglobin desaturation, REM sleep, and deep sleep, and contribute to the reduction of snoring and sleep apnea. We hypothesize that this fact occurred due to cascade effects from stimulation of masticatory muscles (masseter and temporalis muscles), initiating an activation of the upper airway muscular chain, including the oropharyngeal, velopharyngeal, hypopharyngeal, and tongue base muscles. Thus, all these therapies may promote improvements in the stomatognatic system performance. In addition, salivary parameters may also show significant improvement.

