#### Protocol for mastication apparatus

The mastication apparatus (MA) will be used to strengthen, stimulate, and modulate the masticatory muscles, showing a safe, good cost–benefit, and effective myofunctional approach [13, 47]. This MA is composed of two mastication instruments, Hiperboloide® (M.C. CHEIDA—ME, São Paulo, Brazil; http://www.hiperboloide.com), which are fixed in a support rod (SR). This SR is formed from a body of compact or fenestrated thermoplastic material and a stainless-steel wire with two free distal tips to couple the hyperboloids (active tips) (Fig. 8), which was developed by the transdisciplinary team of the CEBAPE-UNESP (the patent process is in progress, under protocol number 18CI038). Mastication apparatus therapy will be performed for 5 min, six times per day, with a minimum interval of 2 h between sessions, and for a period of 2 months. The individuals will simultaneously bite into the two active tips of the MA for 3 s and will release it for 1 s for a total duration of 5 min. This protocol was developed by Giannasi et al. [13]. These patients will be instructed to bite the MA in a slow rhythm. The therapy must be interrupted if the patient complains about feeling pain. After the mechanical exercises, the patients and/or caregivers will be instructed to clean the support rod with running water to remove residual remnants, dry it, and then store it in a safe, fresh, and clean location.

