### Quality control

In order to ensure data quality, the dentists responsible for performing the EMG examination, as well as the sleep technicians responsible for the polysomnography examination, will receive appropriate training. External monitoring will be carried out periodically to verify the performance of EMG and polysomnography.

Guidance on the correct use and performance of each therapy will be given at each appointment, and all participants/caregivers will have access to an exclusive telephone number to solve any doubts they may have during the study, in order to avoid any misunderstanding that may compromise the results. This telephone contact will also be an instrument to reinforce the given guidelines and to encourage adherence to the therapies.

It will be explained to the participants/caregivers that they will be excluded whenever physiotherapy or speech therapy is to be undertaken during the study.

In addition, all participants/caregivers will be aware that they are free to withdraw their participation from this study at any time if they so wish, with no penalties.

If the participants face any difficulties to perform the proposed therapy, then they will be allocated to another therapy that they are able to perform.

The data obtained prior to and 2 months after all proposed therapies will be analyzed by “blind” evaluators. In addition, satisfaction, acceptance, and side effects will be assessed after a 2-month period, for each therapy applied.

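### The Discussion says side effects do not apply, yet the protocol lists them and plans to assess them; the one stated time point, after 2 months, is likely to miss early and temporary ones

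*Protocol article*

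**What the plan says.** In the protocol article, the Discussion asserts that "none of these therapies will cause any injuries to the participants" and concludes that "the hypothesis of harm or of adverse side effects does not apply to the present study".

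The paragraph that follows goes through the therapies one by one:

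- NMES "may produce a feeling of discomfort due to the electrical stimulus applied on masticatory muscles".
- The oral appliance "may initially produce discreet dental and muscular discomfort, with possible temporary hypersalivation and risks of occlusal changes".
- For the third arm: "The mastication apparatus (MA) does not produce discomfort or foreseeable risks".

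Two other sections bear on this. The Protocol for mastication apparatus instructs: "The therapy must be interrupted if the patient complains about feeling pain". Quality control says that "satisfaction, acceptance, and side effects will be assessed after a 2-month period, for each therapy applied", and gives no other time point for side effects. Quality control also allows a participant who has difficulty with the assigned therapy to be moved to another one. It describes a telephone line for questions, guidance and adherence, without mentioning the recording of side effects.

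**The concern.** A protocol cannot set side effects aside as not applicable, name several, and plan to assess them. Whoever runs the trial is told both to look and that there is nothing to find.

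The stated timing adds to this. The Discussion describes the oral appliance's discomfort as arising at the start and its hypersalivation as temporary. An assessment after 2 months comes when such effects may have resolved. Effects troublesome enough to cause withdrawal or a change of therapy are also the ones most easily lost or credited to the wrong arm. At stake is whether the trial's safety data describe what happened during treatment, in adults with Down syndrome for some of whom a responsible person gives consent.

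**Working it through.** **Step 1. Set the statements side by side.**

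| Topic | One place | Another place | Result |
|---|---|---|---|
| Side effects in general | Discussion: not applicable | Discussion, next paragraph: effects listed for NMES and the oral appliance | Contradiction |
| Side effects in general | Discussion: not applicable | Quality control: to be assessed for each therapy | Contradiction |
| Mastication apparatus | Discussion: no discomfort or foreseeable risk | Mastication apparatus section: an instruction for when pain is reported | Tension; a precaution does not prove that pain is expected |
| Oral appliance timing | Discussion: discomfort is early, hypersalivation temporary | Quality control: assessed after 2 months | Poor match for these effects; less so for occlusal change, which is not called temporary |

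**Step 2. Arm size.** The Sample size section gives 10 per group plus 5 for dropout. So 3 × (10 + 5) = 45, which reproduces the stated total. The allowance is 5/15, one third of an arm.

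**Step 3. What a late assessment could lose.** The protocol gives no side-effect rates, so this is an illustration under assumptions. Suppose 20% of an arm of 15 has a transient effect, so 15 × 0.20 = 3 expected. Let q be the share still reported at 2 months. Expected on record is 15 × 0.20 × q, and the chance of recording at least one is 1 − (1 − 0.20q)^15.

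| q | Expected on record | Chance of at least one |
|---|---|---|
| 1.00 | 3.00 | 96.5% |
| 0.75 | 2.25 | 91.3% |
| 0.50 | 1.50 | 79.4% |
| 0.25 | 0.75 | 53.7% |

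Nothing in the protocol fixes q.

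**Step 4. What zero events would mean with complete recording.** The exact upper limit for 0 of n is 1 − 0.05^(1/n) (one-sided 95%) or 1 − 0.025^(1/n) (two-sided 95%).

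| n | One-sided 95% | Two-sided 95% |
|---|---|---|
| 15 | 18.1% | 21.8% |
| 10 | 25.9% | 30.8% |
| 45 (all arms pooled) | 6.4% | 7.9% |

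These limits depend on n alone. They bound what can be claimed and do not measure the recording problem.

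**The case against.** The strongest reply is that this is a loose sentence in a condensed article. It could be meant for serious injury, with the next paragraph covering minor discomfort. That helps only in part, because the sentence names adverse side effects as well as harm.

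Several stronger readings are tempting, and the documents do not support them:

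- **That side effects are assessed at 2 months and at no other time.** The article gives one time point and does not exclude others. Reporting procedures are often left to a full protocol.
- **That assessment rests on recall by people with cognitive impairment.** No informant or method is named; examination is possible, and occlusal change in particular could be examined. Eligibility requires enough preserved cognition to follow verbal commands.
- **That participants who leave early are never asked.** No passage says so. The 5 in 15 is a planning allowance for dropout, not a count of people without side-effect data. The Statistical analysis section has a worst-case rule for missing data. Nothing says that it extends to side effects, and an imputed event would not show what occurred or when.
- **That effects of an abandoned therapy are lost.** Assessing each therapy applied can be read as including one a participant has left.
- **That the trial will under-record harm and then claim safety.** Under-recording is likely, not shown. Tolerance is already noticed in care: NMES current depends on patient sensitivity, and titration uses reports from patients and caregivers. No safety endpoint or no-harm conclusion is planned. The wording that NMES is safe cites earlier work.
- **That the pain instruction flatly contradicts the Discussion.** It is a precaution that sits uneasily with the claim of no discomfort.

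The contradiction between the no-harm sentence, the list that follows it and the planned assessment survives all of this. So does the poor match between the one stated time point and effects described as early or temporary.

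**Conclusion.** The point holds in this form. The Discussion contradicts itself and Quality control on whether side effects apply, and its statement on the mastication apparatus needs reconciling with the pain instruction. This rests on published text, so a fuller document would not remove it.

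The second part is conditional. If assessment after 2 months is the working rule, it is likely to under-record early and temporary effects, and those in participants who withdraw or change therapy. The size is unknown; the 20% rate and the values of q above are assumptions. A full protocol with ongoing reporting would largely answer this part.

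Separately, arms of 10 to 15 cannot support a categorical statement of no injury, however good the recording. Zero events would leave rates up to 26% or 18% open (one-sided 95%).

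**What to change.** 1. Delete the sentence that harm and side effects do not apply. Reconcile the Discussion, Quality control and Protocol for mastication apparatus sections on discomfort, pain and the assessment of side effects. Which clinical statement is right is for the investigators to settle.
2. Record side effects from first use of therapy on one common short form at contacts that already exist: the three weekly NMES sessions, the weekly or biweekly appliance titration, appointments, and the telephone line. Keep the assessment after 2 months. Include participants who stop or change therapy.
3. Report the number of participants with each effect by randomised arm, noting the therapy in use at onset, with exact 95% confidence intervals. Limit any safety statement to those intervals.

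Contacts are more frequent in some arms than others, so the report should state how often each arm was asked; otherwise an arm seen more often may look worse.

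The cost is a short form at existing contacts, a few lines in the report and a wording change. No visits or staff are added, and the sample size is unaffected.

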## Abbreviations

DS: Down syndrome
MA: Mastication apparatus
NMES: Neuromuscular electrical stimulation
OA_m_: Mandibular advancement oral appliance
OSA: Obstructive sleep apnea
PSG: Polysomnography
sEMG: Surface electromyography
SR: Support rod
